#### Blood test

Complete blood count (CBC), BUN and creatinine (Cr) will be evaluated at 1-2 week before, and weekly during radiotherapy. Serum albumin will be collected at 1-2 week before and first, third and seventh week of radiotherapy.

#### ECOG performance status

ECOG performance status will be assessed at 1 week before, weekly during radiotherapy, and 1 month after radiotherapy.

|   |                                                                                                                                                           |
|---|-----------------------------------------------------------------------------------------------------------------------------------------------------------|
| 0 | Fully active, able to carry on all pre-disease performance without restriction.                                                                           |
| 1 | Restricted in physically strenuous activity but ambulatory and able to carry out work of a light or sedentary nature, e.g., light housework, office work. |
| 2 | Ambulatory and capable of all selfcare but unable to carry out any work activities. Up and about more than 50% of waking hours.                           |
| 3 | Capable of only limited selfcare, confined to bed or chair more than 50% of waking hours.                                                                 |
| 4 | Completely disabled. Cannot carry on any selfcare. Totally confined to bed or chair.                                                                      |
| 5 | Dead                                                                                                                                                      |

#### Weight and Height

Weight and height will be measured weekly during radiotherapy. Body mass index (BMI) will be calculated by weight (kg) divided by square of height in centimeters.

$$BMI = \frac{\text{weight (kg)}}{[\text{height (cm)}]^2}$$

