### Secondary objective

1. To determine whether immunonutrition can reduce inflammation and increase immunity during radiotherapy.
2. To compare other acute side effects during radiotherapy between two arms.
3. To evaluate nutrition status during radiotherapy.

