## Population

Locally advanced head neck cancer patient treating with definitive or postoperative concurrent chemoradiotherapy in:

- Division of Radiation Oncology, Faculty of Medicine, Chiang Mai University.
- Radiotherapy section, Udonthani Cancer Hospital
- Radiotherapy section, Lampang Cancer Hospital

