### Radiotherapy

Patient will be treated with radiotherapy in 3D conformal or IMRT/VMAT/Tomotherapy technique. Dose of radiotherapy to primary tumor, negative margin tumor bed, and close or positive margin tumor bed are 70, 60, and 66 Gy, respectively. Dose and area of neck node irradiation depend on physician judgement.

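### BMI is defined with height in centimetres, and the mid-treatment albumin sample is set for week 3 in the text but week 4 in the schedule

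*Protocol*

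**What the plan says.** The third secondary objective in the protocol reads: "To evaluate nutrition status during radiotherapy". It names no measure, but the assessment sections provide weight, height, BMI and serum albumin, which bear on it.

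- **BMI (Weight and Height).** "Body mass index (BMI) will be calculated by weight (kg) divided by square of height in centimeters". The equation below the sentence has the same denominator, height in cm, squared.
- **Albumin, text (Blood test).** "Serum albumin will be collected at 1-2 week before and first, third and seventh week of radiotherapy".
- **Albumin, schedule (table under Nutritional status).** The albumin row is marked at the pre-radiotherapy visit and at weeks 1, 4 and 7. Weeks 2, 3, 5 and 6 are blank.
- **Treatment length (Radiotherapy).** "Dose of radiotherapy to primary tumor, negative margin tumor bed, and close or positive margin tumor bed are 70, 60, and 66 Gy, respectively". Neither the dose per fraction nor the number of fractions per week is given. The Population section admits both definitive and postoperative patients.

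**The concern.** The BMI rule gives a wrong value if followed literally. The unit appears in words and again in the equation, so it cannot be put down to a misread character. Anyone programming the variable from the protocol would produce figures that are not BMI on its usual kg/m² scale.

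The albumin rule gives two dates for one sample. With three centres taking part, staff could reasonably work from either the text or the table. The complete blood count is scheduled every week, so the other blood tests give no cue as to which albumin week is meant. A mid-treatment summary could then combine samples taken a week apart, and this could not be repaired afterwards.

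At stake are the correctness of the reported BMI values and the comparability of one albumin time point. Both serve a stated secondary objective.

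**Working it through.** The protocol reports no BMI value, so there is no figure of its own to reproduce. The check applies the rule as written and sets the two albumin schedules side by side.

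**1. BMI**

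As written: weight (kg) / [height (cm)]². In kg/m²: weight (kg) / [height (m)]². Since height (cm) = 100 × height (m), the two differ by 100² = 10,000 for every patient. The weights and heights below are illustrative assumptions.

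| Weight, height | As written | Height in metres |
|---|---|---|
| 55 kg, 160 cm | 55 / 25,600 = 0.0021 | 55 / 2.56 = 21.5 |
| 45 kg, 150 cm | 45 / 22,500 = 0.0020 | 45 / 2.25 = 20.0 |
| 60 kg, 165 cm | 60 / 27,225 = 0.0022 | 60 / 2.7225 = 22.04 |
| 80 kg, 180 cm | 80 / 32,400 = 0.00247 | 80 / 3.24 = 24.69 |

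**2. Albumin**

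The albumin row, read cell by cell against the table header:

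| Source | Pre-RT | Wk 1 | Wk 2 | Wk 3 | Wk 4 | Wk 5 | Wk 6 | Wk 7 |
|---|---|---|---|---|---|---|---|---|
| Blood test section | x | x | | x | | | | x |
| Schedule table | x | x | | | x | | | x |

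The two agree on the pre-radiotherapy sample, week 1 and week 7. They conflict on the single sample between. The albumin row has its full number of cells and lines up with the complete blood count and BUN/creatinine rows above it, so a broken table is an unlikely explanation.

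**3. Week 7 and treatment length (conditional)**

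Fractionation is not stated, so this step rests on an assumption: five fractions per week and 1.8 to 2.2 Gy per fraction. Fractions = dose / dose per fraction, rounded up; weeks = fractions / 5, rounded up.

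| Total dose | 1.8 Gy | 2.0 Gy | 2.2 Gy |
|---|---|---|---|
| 60 Gy | 34 fractions, 7 weeks | 30 fractions, 6 weeks | 28 fractions, 6 weeks |
| 66 Gy | 37 fractions, 8 weeks | 33 fractions, 7 weeks | 30 fractions, 6 weeks |
| 70 Gy | 39 fractions, 8 weeks | 35 fractions, 7 weeks | 32 fractions, 7 weeks |

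Depending on the assumption, a 60 Gy course ends in week 6 or week 7. These figures show the range only and say nothing about how treatment should be given.

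**The case against.** The strongest reply is that neither slip damages a comparison the trial depends on.

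- **BMI.** A constant factor of 10,000 leaves between-arm tests and percentage changes unchanged. The protocol uses no BMI cut-off for eligibility, stratification, endpoints or analysis. Weight and height are both recorded weekly, so BMI can be recomputed without loss. All of this stands. It limits the consequence to reported values but does not make the definition correct.
- **Albumin.** Nothing shows that centres would in fact diverge. If they did, randomization is stratified by centre, so a difference in week between centres would mainly add noise and would not bias one arm. This also stands. The contradiction remains, and a sample taken in a different week cannot be recovered.
- **Scope.** Neither BMI nor albumin is a listed endpoint, and weekly weight is specified consistently during radiotherapy. A reader might infer that the nutrition measures as a whole are wrong, or that the third secondary objective fails. The documents do not support that: the fault lies in one unit and one week.
- **Week 7.** A reader might also infer that the fixed week-7 sample is an error that leaves patients on the shortest course without an end-of-treatment albumin. The protocol never calls that sample an end-of-treatment value; it is simply the last one scheduled. Whether any patient lacks a week 7 depends on fractionation that is not stated, and the share of 60 Gy patients is unknown. Any gap would follow dose, not randomized arm. Tying the sample to the last week of radiotherapy would be a design choice, and it would pool samples taken in different weeks.

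**Conclusion.** Two misstatements hold, and both can be read directly from the current text. BMI as defined is 10,000 times too small for every patient. The one mid-treatment albumin sample has two incompatible dates, a week apart. Neither conclusion depends on an assumption; the body sizes used above are only illustrations.

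The impact is minor. It reaches the reported BMI values and the comparability of one albumin value across centres. It does not reach the primary endpoint, the listed secondary outcomes, the sample size or weekly weight, and no bias between arms is shown.

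The week-7 sample deserves a conditional remark only. If 60 Gy is given as 2 Gy five times a week, those patients finish in week 6, and the protocol does not say how the last albumin sample applies to them. Over 1.8 to 2.2 Gy per fraction the same dose takes 6 to 7 weeks, so this is not established as a defect.

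**What to change.** 1. In Weight and Height, change the sentence and the equation to weight (kg) / [height (m)]².
2. Reconcile the Blood test section with the schedule table so that a single mid-treatment albumin week applies at all three centres. The sponsor must settle which week is intended; the documents do not show it. If samples have already been taken, record the actual week of each.
3. Optionally, state how the last albumin sample applies to a patient whose radiotherapy does not end in week 7.

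Items 1 and 2 are wording corrections and add no samples. Item 3 is a clarification; whether it adds a sample for some patients depends on what the sponsor decides. Item 2 is the one to settle promptly, since BMI can be recomputed at any time from the recorded weight and height.

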#### Nutritional status

All patients will receive nutrition consultation every visit.

| Items            | Screening | 1-2 week before RT | Week during radiotherapy |   |   |   |   |   |   |
|------------------|-----------|--------------------|--------------------------|---|---|---|---|---|---|
|                  |           |                    | 1                        | 2 | 3 | 4 | 5 | 6 | 7 |
| Informed consent | x         |                    |                          |   |   |   |   |   |   |
| Demographic data | x         |                    |                          |   |   |   |   |   |   |
| Randomization    | x         |                    |                          |   |   |   |   |   |   |
| CBC              |           | x                  | x                        | x | x | x | x | x | x |
| BUN/Cr           |           | x                  | x                        | x | x | x | x | x | x |
| Albumin          |           | x                  | x                        |   |   | x |   |   | x |

|        |  |   |   |   |   |   |   |   |   |
|--------|--|---|---|---|---|---|---|---|---|
| CTCEA  |  | x | x | x | x | x | x | x | x |
| Weight |  | x | x | x | x | x | x | x | x |
| Height |  | x | x | x | x | x | x | x | x |

## Discontinuation/withdrawal of the volunteer from the study

The volunteer may with be withdrawn from the study anytime including:

- Patient withdraws consent (reason for withdrawal will be documented)
- Ineligibility (either arising during the study or retrospectively was overlooked at Screening)
- Significant non-compliance with treatment regimen or study requirements in inability to continue to comply with study procedures.
- An adverse event, which is deemed by the treating physician to compromise the safety of the subject, including grade III-IV toxicity caused by the study product.

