## Eligibility

### Inclusion criteria

1. Age range between 18 – 70-year-old
2. Histologically confirmed squamous cell carcinoma of head and neck.
3. Locally advanced head and neck cancer planning to treat with concurrent chemoradiotherapy for definitive or postoperative setting.
4. No previous radiotherapy in head and neck area.
5. Good performance status with ECOG 0-1.
6. Laboratory tests are in the normal ranges.
7. The participant or legal representative provides the written informed consent for the study.

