## Material and Method

### Recruitment and Informed Consent process

Potential volunteer who is met the inclusion criteria and not in exclusion criteria will be fully explained about the study by the investigator. The volunteer will have the sufficient time to read informed consent and have the opportunity to ask any question that may have. He/she also can ask the relative or someone he/she trusts about sign the informed consent form and is informed that the process is voluntary and can be withdrawn anytime. After fully understanding and accepting to join the study, he/she will sign the informed consent form that is approved by the local ethical committee.

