### Chemotherapy

Platinum-based chemotherapy (cisplatin 40 mg/m^2 or carboplatin AUC 2) will be given in weekly basis during radiotherapy.

Induction chemotherapy or adjuvant chemotherapy is allowed. The induction/adjuvant chemotherapy regimen is based on each institutional practice.

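### Withdrawal for ineligibility that arises on study, read with undated ECOG and laboratory criteria, lets a counted toxicity serve as a ground for leaving the study, and nothing keeps gradings going afterwards

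*Protocol*

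**What the plan says.** - **Protocol, Discontinuation/withdrawal of the volunteer from the study.** A volunteer may "be withdrawn from the study anytime including" four listed grounds, the second of which is "Ineligibility (either arising during the study or retrospectively was overlooked at Screening". The rule is permissive, and what ends is study participation, not only the supplement.
- **Protocol, Inclusion criteria.** Criterion 5 is "Good performance status with ECOG 0-1" and criterion 6 is "Laboratory tests are in the normal ranges". Neither has a time point, and criterion 6 names no tests.
- **Protocol, Blood test and ECOG performance status.** "Complete blood count (CBC), BUN and creatinine (Cr) will be evaluated at 1-2 week before, and weekly during radiotherapy". ECOG is also scored weekly during radiotherapy and again one month later.
- **Protocol, Side effect evaluation and Secondary Outcomes.** Anaemia and low white cell, neutrophil, lymphocyte and platelet counts are among the weekly graded toxicities. The first secondary outcome compares grade 2-4 toxicities by site or system.
- **Protocol, schedule table under Nutritional status.** CBC and CTCAE grading are marked for every week of radiotherapy to week 7.
- **Protocol, Primary endpoint.** Grade 2-4 oral mucositis during radiotherapy. Mucositis appears in no eligibility criterion.

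No section says that gradings continue in a participant who has been withdrawn.

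**The concern.** The withdrawal ground has two limbs: an error at entry that is found later, and ineligibility that develops later. The second needs criteria that can cease to be met. Criteria 5 and 6 are such criteria, and the treatment is expected to change both, since all participants receive weekly platinum with radiotherapy. The same blood count can therefore be an outcome to be graded and a reason to stop grading.

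A participant withdrawn in, say, week 2 for a count just below normal might never have the grade 2 haematologic toxicity that the secondary outcome counts recorded. The mucositis gradings of weeks 3 to 7 would be lost as well. Such loss would be related to toxicity, left to discretion and decided by unblinded staff at three centres. An analysis plan can choose how to treat missing gradings, but it cannot recover gradings that were never taken.

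**Working it through.** **Step 1. The sections side by side.**

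| Measure | Eligibility | Re-measured | Counted as outcome | Withdrawal ground if read literally |
|---|---|---|---|---|
| Blood counts | Criterion 6, undated | Weekly | Yes, haematologic toxicity | Yes |
| ECOG | Criterion 5, undated | Weekly | Not a listed endpoint | Yes |
| Oral mucositis | None | Weekly | Yes, primary | No; only indirectly, through ECOG or a low count |

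The direct overlap is with the haematologic outcomes. Nothing says that data recorded before withdrawal are discarded, so what is at risk is the later weeks.

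**Step 2. The plan's own figure.** Inputs from Sample size: p1 = 0.61, p2 = 0.305, power 0.80, and 0.05 (printed as beta, read as two-sided alpha). With mean p = 0.4575:

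n = [1.96·√(2·0.4575·0.5425) + 0.842·√(0.61·0.39 + 0.305·0.695)]² / 0.305² = 41 per arm, and 41/0.85 gives 49.

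Both stated figures reproduce. Neither depends on the withdrawal rule.

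**Step 3. Loss unrelated to outcome.** With m = 50(1 − loss) per arm,

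power = Φ{[0.305·√m − 1.96·√(2·0.4575·0.5425)] / √(0.61·0.39 + 0.305·0.695)}.

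| Loss | m | Power |
|---|---|---|
| 0% | 50 | 0.876 |
| 15% (planned) | 42.5 | 0.817 |
| 20% | 40 | 0.793 |
| 30% | 35 | 0.736 |
| 40% | 30 | 0.667 |

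The 15% allowance leaves little margin: power is below 0.80 at 20% total loss.

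**Step 4. Loss related to outcome (assumed, same in both arms).** Let a share f of would-be grade 2+ mucositis cases leave before the event is recorded. If they count as event-free, the observed rate is p(1 − f). If they are excluded, it is p(1 − f)/(1 − pf).

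| f | Event-free: control v IN | Power | Excluded: control v IN | Power |
|---|---|---|---|---|
| 10% | 54.9% v 27.5% | 0.81 | 58.5% v 28.3% | 0.86 |
| 20% | 48.8% v 24.4% | 0.72 | 55.6% v 26.0% | 0.83 |
| 30% | 42.7% v 21.3% | 0.63 | 52.3% v 23.5% | 0.80 |

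At f = 20% the difference falls from 30.5 points to 24.4 (48.8 − 24.4) in one case and to 29.6 (55.6 − 26.0) in the other. The risk ratio stays at 0.50 in the first and becomes 26.0/55.6 = 0.47 in the second.

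**Step 5. Unequal loss (assumed).** Suppose 30% of controls and 15% of IN participants are withdrawn, carry 1.3 times their arm's average mucositis risk, and are excluded. The observed rate is p(1 − 1.3w)/(1 − w): 0.61·0.61/0.70 = 53.2% and 0.305·0.805/0.85 = 28.9%, with power 0.586.

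With no true effect (61% in both arms), a risk of 70% in withdrawn patients and the same withdrawal rates, control shows (0.61 − 0.30·0.70)/0.70 = 57.1% and IN (0.61 − 0.15·0.70)/0.85 = 59.4%. That is a spurious 2.3 points against IN. Exchanging the two withdrawal rates reverses the sign.

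The documents supply no value for f, for w or for the excess risk.

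**The case against.** The case on the other side is substantial.

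- **The rule says may.** A reader might infer that outcome data stop once toxicity begins. The text only permits withdrawal, so that inference fails.
- **The rest of the protocol implies that patients with toxicity stay.** Counts and gradings run to week 7, and the full ECOG scale is reproduced. Nutrition support has participants with intake-limiting symptoms treated. The adverse-event withdrawal ground is confined to events that compromise safety, a limit with little purpose if any abnormal value sufficed. This shows the probable intent. It also shows that the ineligibility ground, as written, conflicts with that intent.
- **Eligibility is described at recruitment.** The protocol says "Potential volunteer who is met the inclusion criteria and not in exclusion criteria will be fully explained about the study by the investigator". That section governs entry and does not limit the withdrawal section. An entry-only reading of every criterion would leave the limb on ineligibility arising later with no work to do.
- **That limb has ordinary uses.** Pregnancy or new metastatic disease can arise on study. This stands, and is why simply deleting the phrase would go too far.
- **Heavier loss among controls is not established.** A reader might infer it from the earlier trials cited in the Literature Review, which report less haematologic toxicity with IN. The first reports this for grade 3-4, which says little about values merely outside normal. The team's in-house evaluation found no better lymphocyte count or neutrophil-to-lymphocyte ratio overall, with a higher lymphocyte count only at the end of radiotherapy in the head and neck subgroup. The second trial found no difference in non-haematologic toxicity, so nothing supports a particular excess mucositis risk in withdrawn patients.
- **Induction chemotherapy.** "Induction chemotherapy or adjuvant chemotherapy is allowed", so a reader might picture a participant randomised, then given induction, who reaches radiotherapy already outside the normal range. No section fixes that order.

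What remains is the permission itself and the absence of any provision for grading after withdrawal.

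**Conclusion.** The point holds as a conflict within the protocol. A low count or an ECOG decline is a permitted ground for leaving the study, low counts are also outcomes, and no section preserves gradings afterwards. The direct effect is on the haematologic secondary outcomes; the primary endpoint is exposed only through missing later weeks.

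No size or direction of bias follows from the documents. The calculations show only that the result depends on unstated quantities: how many leave, whether the arms differ, whether grade 2 mucositis had already been recorded, and how those who leave are analysed. A reader might conclude that the primary comparison is biased against IN, or that the three centres will produce different data. Both are possible, but neither is shown. This is a cheap improvement that removes an avoidable risk, not a demonstrated failure of the design. How an analysis plan would handle missing data is not at hand and is not counted against the protocol.

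**What to change.** Reconcile the withdrawal section with Inclusion criteria, Side effect evaluation, Blood test, ECOG performance status and the schedule table:

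1. State that criteria 5 and 6 are judged at entry, for eligibility.
2. Separate stopping the study product from leaving the study.
3. Continue the weekly CTCAE gradings and the PRO-CTCAE ratings to the end of radiotherapy for every randomised participant who has not withdrawn consent, including those found to be or becoming ineligible, and analyse them in the randomised arm.
4. Leave clinical decisions, and grounds such as pregnancy or new metastasis, with the treating physician.

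The cost is a short amendment and continued data entry at visits already scheduled. It needs no added tests or participants.

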## Statistical Consideration

### Study Endpoint

#### Primary endpoint

1. Difference of the proportion of grade 2-4 CTCEA toxicities of oral mucositis during radiotherapy between IN arm and control arm.

#### Secondary Outcomes

1. Difference of the proportion of remaining grade 2-4 CTCEA toxicities of each site/system of between 2 arms.
2. Difference of the proportion of remaining cumulative grade 2-4 PRO-CTCEA toxicities of oral mucositis and radiation dermatitis of between 2 arms.

### Sample size

Based on our previous study on concurrent chemoradiotherapy (CCRT) in nasopharyngeal cancer, incidence of grade  $\geq 2$  oral mucositis according to CTCEA version 3 in CCRT and adjuvant chemotherapy was 61%. The effect of IN on oral mucositis from a metaanalysis by Zheng et al. showed that risk ratio of grade  $\geq 3$  was 0.45 (95% confident interval 0.22–0.92). We assume that IN will half the incidence of oral mucositis to 30.5%. With the power of 0.8 and beta of 0.05, the sample size is calculated to be 41 per arm. With 15% drop out rate is considered, the sample size per arm will be 49.

We will consider rounding up and including 50 participants per arm, the total participants in this study will be 100.

